**Methods/Design:**

SPARC is a “rolling-six” design single-arm study to establish the maximum tolerated dose for margin-intensive stereotactic radiotherapy before resection of pancreatic cancer at high risk of positive resection margins. Eligible patients will have histologically or cytologically proven pancreatic cancer defined as borderline-resectable per National Comprehensive Cancer Network criteria or operable tumour in contact with vessels increasing the risk of positive margin. Up to 24 patients will be recruited from up to 5 treating centres and a ‘rolling-six’ design is utilised to minimise delays and facilitate ongoing recruitment during dose-escalation. Radiotherapy will be delivered in 5 daily fractions and surgery, if appropriate, will take place 5–6 weeks after radiotherapy. The margin-intense radiotherapy concept includes a systematic method to define the target volume for a simultaneous integrated boost in the region of tumour-vessel infiltration, and up to 4 radiotherapy dose levels will be investigated. Maximum tolerated dose is defined as the highest dose at which no more than 1 of 6 patients or 0 of 3 patients experience a dose limiting toxicity. Secondary endpoints include resection rate, resection margin status, response rate, overall survival and progression free survival at 12 and 24 months. Translational work will involve exploratory analyses of the cytological and humoral immunological responses to stereotactic radiotherapy in pancreatic cancer. Radiotherapy quality assurance of target definition and radiotherapy planning is enforced with pre-trial test cases and on-trial review. Recruitment began in April 2015.

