Pre-operative (chemo) radiotherapy aims to treat the tumour in situ to achieve tumour regression and facilitate curative resection. This approach has become standard of care for some tumour sites, having been shown to reduce local recurrence in rectal cancer [17], and increase overall survival in oesophageal cancer [18], but is not established in pancreatic cancer due to limited effectiveness of standard dose schedules, despite potential advantages over postoperative treatment [19]. A complete tumour response is only seen in around 5 % of patients [20], though a larger proportion of patients (35 %) benefit from tumour down-staging to achieve resectability [21] and patients who successfully complete neoadjuvant chemoradiotherapy and go on to have resection tend to have high rates of clear resection margins [22, 23] and reduced rates of local recurrence [24, 25].

Stereotactic body radiation therapy (SBRT) combines rigorous immobilisation and image-guidance with hypofractionation, to reduce radiotherapy planning margins and treat small targeted volumes with greater accuracy and precision, supporting safe delivery of much higher biologically effective doses. It has been shown to be a highly-effective local treatment option in unresectable pancreatic cancer with high rates of local control achieved using treatment delivered in a single exposure [26–29], and when treatment was delivered in 3–5 fractions lower rates of toxicity were seen without compromising disease control [30–35].

The specific goal in treating BRPC with pre-operative radiotherapy will be improve the chances of achieving clear resection margins, reduce risk of local recurrence and achieve chances of long-term survival similar to those for patients with initially resectable tumours. Neoadjuvant treatment has been shown to be deliverable and effective in BRPC, such as in a series of 160 patients described by Katz et al., among whom 78 % completed preoperative therapy and restaging, and 41 % underwent pancreatectomy, with a 94 % rate of clear margins [36].

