### Outcome measures and definitions

The primary endpoint of the SPARC study is MTD, defined as the highest level of SBRT at which no more than 1 of 6 patients or 0 of 3 patients experiences a DLT in the period from starting SBRT to one month post-surgery or one month after the evaluation in week 3 post-SBRT if no surgery takes place. DLT is defined as these possible adverse events (AEs) (according to CTCAE v4.03), seen in the DLT assessment period:≥ Grade 3 upper gastro-intestinal (GI) bleeding≥ Grade 4 nausea/vomiting uncontrolled after 48 h of standard treatment≥ Grade 4 pancreatitis not stent relatedInterruption of SBRT >1 week due to SBRT-related AEs≥ Grade 4 vascular events: SMV thrombosis, bowel ischaemia due to SMA arteritis/stenosis, friable vessels at surgeryOther AEs that the TMG agrees to be dose limiting and possibly related to SBRT such as ≥ grade 3 gastrointestinal fistula >30 days after surgery

Secondary outcomes include resection rate, resection margin status rates, rate of pathological complete response, late SBRT toxicity, efficacy and long term safety. Resection rate is defined as the proportion of patients with radical oncological resection of pancreatic cancer over the total enrolled patients. Resection margin status (R0/R1/R2) is defined according to the standards of the Royal College of Pathologists, and response rate is defined as the rate of patients with pathological complete response over the total enrolled patients. Late toxicity is defined as any GI AE/other AE > grade 2 occurring between 1 month and 6 month post-surgery. Additional secondary outcomes include efficacy and long term safety as indicated by progression free survival (PFS) and overall survival (OS). PFS is defined as the time from date of first SBRT dose to the first date of progression or death for any cause, or is censored at the date of last known follow-up date if they are not observed to die during the course of the trial. OS is defined as the time from date of first SBRT dose to the date of death for any cause or is censored at the last known follow-up date. Exploratory outcomes include relationships between imaging and pathology (treatment response and resection margin status) and changes in markers of the innate and adaptive immune response before and during SBRT (cytological assessments and levels of interferon-related RNA).

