### Sample size considerations

Patient numbers will be determined by the primary endpoint of establishing the MTD, which will require a maximum of 24 evaluable patients. An evaluable patient for primary endpoint analysis is defined as one who has received at least one fraction of SBRT and experiences a DLT, or a patient who has received at least four fractions of SBRT and is assessed one month post-surgery (or assessed at similar time for DLT if no surgery). Patients not evaluable for primary endpoint will be replaced, but a patient who does not become evaluable for the primary endpoint may continue to be followed up for surgical outcome, PFS and OS as appropriate, unless consent is withdrawn.

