### Statistical analysis

All analyses will follow a statistical analysis plan written in accordance with current standard operating procedures. Baseline characteristics will be summarised (number/frequency) for all enrolled patients. Patients who died or withdrew before treatment started or fail to complete the required safety observations will be described separately. Primary MTD analysis will concern the frequency of patients with no DLT according to dose-escalation of SBRT. Descriptive statistics will summarise the DLT’s and safety variables with patients grouped according to dose level received. Secondary outcomes (resection rate, resection margin status and response rate) associated with SBRT will be summarised by descriptive statistics along with numbers and percentages. Late toxicity will be summarised by descriptive statistics for all patients who received at least one dose of SBRT treatment. Physical exam, haematology and biochemistry data will be summarised across time. Both PFS and OS estimates at one and two years and 90 % CI will be provided together with median estimates. A Kaplan-Meier curve will be plotted with 90 % CI. A trial summary will record patient recruitment and trial decision-making.

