MDACC criteria. Most patients received Gemcitabine-based systemic chemotherapy. The SBRT consisted of 24–36 Gy in 3 fractions, surgery took place at a median 3.3 months (range 1.5 – 6.6 months) and 11/12 patients had an R0 resection. Chuong et al. [39] treated 73 patients (of which 57 were deemed BRPC using NCCN criteria) with systemic Gemcitabine-based chemotherapy and 5-fraction SBRT. Median dose prescribed was 35 Gy to the tumour margin and no less than 25 Gy to the entire pancreatic tumour. 44/57 BRPC cases underwent exploratory resection and 31/32 resected cases had an R0 resection. No acute toxicity > grade 3 occurred and 5.3 % (4 patients with locally advanced inoperable disease) experienced late grade 3 toxicity (3 GI bleeding and 1 anorexia). With a median FU of 10.5 months (2.2‐25.9 months) the median OS was 16.4 months in all BRPC patients, with median OS of 19.3 months in resected patients. Disappointing overall survival rates in published series (median overall survival 5–20 months) are attributed to variable provision of optimal systemic treatment.

Evidence is growing for the importance of Radiation Therapy Quality Assurance (RTQA) for clinical trial interpretation as well as patient outcomes [40]. The SPARC trial incorporates a comprehensive prospective RTQA programme with a detailed radiotherapy protocol and atlas that was supported by a pre-trial workshop for collaborating clinicians, both of which have been shown to reduce variation in target volume definition [41–43]. A pre-trial test case of contouring and planning must be completed satisfactorily by recruiting centres and RTQA will continue with on-trial peer review prior to treatment supported by web-conferencing facilities.

The trial originally opened with eligibility criteria that excluded patients with suspicion of metastatic disease, those who may not be fit for surgical resection, and those who had received induction chemotherapy, which has become more common practice since the study was initially designed. Many patients presenting to our centre with BRPC were rendered ineligible for these reasons, and during the first year that the trial was open only one patient was successfully recruited. The primary endpoint of the study is the assessment of the safety and tolerability of the intervention, and therefore the patient eligibility inclusion and exclusion criteria for the study were revised to the current version published here, with the aim of improving patient recruitment.

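### Late toxicity is dated only from surgery but summarised over all SBRT-treated patients, so a patient who has no operation counts in the population yet cannot have an event

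*Protocol article*

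**What the plan says.** Under Outcome measures and definitions, the late-toxicity endpoint is fixed by grade and by time since surgery: "Late toxicity is defined as any GI AE/other AE > grade 2 occurring between 1 month and 6 month post-surgery". No other starting date is given. Under Statistical analysis, the population is wider than the operated patients: "Late toxicity will be summarised by descriptive statistics for all patients who received at least one dose of SBRT treatment".

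The article does not expect every treated patient to be operated on. The abstract's Methods/Design paragraph says "surgery, if appropriate, will take place 5–6 weeks after radiotherapy".

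Two neighbouring rules provide for patients without surgery. The DLT period closes "one month after the evaluation in week 3 post-SBRT if no surgery takes place", and the evaluability rule under Sample size considerations adds "or assessed at similar time for DLT if no surgery". The late-toxicity definition has no such clause.

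**The concern.** The event definition and the analysis population do not fit together. A treated patient who never has surgery is in the population, but no event in that patient can meet the definition. Because the DLT and evaluability rules both foresee this patient, the gap is a mismatch between two stated rules and not merely detail left out of a condensed article.

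Late SBRT toxicity is a named secondary outcome of a dose-finding trial whose MTD is meant to go forward to a phase II study (Conclusion). For a patient without surgery, a grade 3 or worse event after the DLT period is neither a DLT nor late toxicity. A dose level with few operations could therefore look cleaner than one with many, for a reason unrelated to dose.

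The group may not be small. The Background says many patients with localised disease soon develop metastases and can be spared surgery. Table 1 admits patients with uncertain metastatic status.

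**Working it through.** **Inputs from the article**

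- Maximum sample: "which will require a maximum of 24 evaluable patients" (Sample size considerations). Check: 4 dose levels × 6 patients = 24, which reproduces the figure. Non-evaluable patients are replaced, so the number with at least one SBRT dose may be somewhat higher.
- Share operated on, higher assumption: in the five-fraction SBRT series described in the Discussion, 44 of 57 borderline-resectable patients were explored. 44/57 = 77%, leaving 13/57 = 23% with no operation.
- Share operated on, lower assumption: 41% had pancreatectomy in the series of 160 described in the Background. Patients explored but not resected are not reported there, so 41% is a lower bound on the share operated on in that series. Only 78% of that series "completed preoperative therapy and restaging", so its denominator is not a population defined by having received SBRT.

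**Inputs assumed**

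- The article gives neither a true late-toxicity risk nor an expected operation rate. I use risks of 10% and 20%, equal in operated and unoperated patients, and operated shares of 77% and 41%.
- Exploration without resection counts as surgery, since it supplies a surgery date.

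**When the DLT period ends without surgery**

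3 weeks + one month = 21 + 30 = about 51 days after SBRT.

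**Dilution**

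Let s be the share operated on, p_o the risk in operated patients and p_u the risk in unoperated patients.

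- True rate = s × p_o + (1 − s) × p_u
- Rate under the current text = s × p_o
- Amount missed = (1 − s) × p_u

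With equal risk p, the reported rate is s × p. The chance of at least one event in a level of six is 1 − (1 − p)^6 for the true risk and 1 − (1 − s × p)^6 under the current text.

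| | All have a window | s = 77% | s = 41% |
|---|---|---|---|
| Patients of 24 with no window | 0 | 24 × 13/57 = 5.5 | 24 × 0.59 = 14.2 |
| Reported rate, true 10% | 10% | 7.7% | 4.1% |
| Reported rate, true 20% | 20% | 15.4% | 8.2% |
| Expected events in 24, true 10% | 2.4 | 1.85 | 0.98 |
| At least one event in six, true 10% | 47% | 38% | 22% |
| At least one event in six, true 20% | 74% | 63% | 40% |

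If surgery were read to mean resection only, the SBRT series would give s = 32/57 = 56%, and a true 10% would read as 5.6%. This lies inside the range shown.

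**The case against.** **No percentage is promised.** For resection rate, margin status and response rate the article mentions numbers and percentages. For late toxicity it says only descriptive statistics, and a SAP governs the analyses. This stands in part: the dilution arises once events are set against the stated population. However, that population is stated, and the event definition excludes some of its members whatever summary is used.

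**Later events may still be reported.** Statistical analysis also summarises safety variables by dose level, so a late event in an unoperated patient need not vanish. This stands, and it lowers the severity. The event would still be absent from the late-toxicity endpoint.

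**The net bias for SBRT-caused toxicity is unknown.** The definition counts any qualifying event without attribution, so complications of surgery count in operated patients. This stands. The downward direction holds for the endpoint as defined, not for toxicity attributable to SBRT.

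**Stronger readings are not supported.**

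- A reader might infer that every unresected patient lacks a window. Patients explored but not resected have a surgery date. In the SBRT series these were 44 − 32 = 12 of 57.
- A reader might also infer that late events concentrate in unresected trial-type patients, so that the reported rate could be 0%. The four late events in that series were in "patients with locally advanced inoperable disease) experienced late grade 3 toxicity", which places them outside its 57 borderline-resectable patients. The article reports no late grade 3 event among the 57 − 32 = 25 borderline-resectable patients who were not resected. The four events show that late toxicity can occur without surgery, and nothing about its concentration in this trial's population.

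**Conclusion.** The late-toxicity endpoint is wrong as written, with moderate severity. Patients who have no surgery at all are in the analysis population but cannot have an event. From about 51 days after SBRT, their grade 3 or worse events fall in neither the DLT nor the late-toxicity endpoint.

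For the endpoint as defined, the direction is certain whenever unoperated patients carry any late risk. The size is not known. With equal risk and 77% to 41% operated on, a true 10% reads as about 7.7% to 4.1%. Both shares come from other series and the 10% is assumed, so this is a range for illustration and not a forecast.

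A reader might infer that the dose decision is compromised. It is not: the MTD rests on the DLT period, which does provide for patients without surgery.

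**What to change.** Reconcile Outcome measures and definitions with Statistical analysis in one of two ways.

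1. Preferred: for patients without surgery, start the late-toxicity window when their DLT period ends and close it at an equivalent time counted from SBRT. All patients with at least one SBRT dose who enter a window can then form the denominator.
2. Alternative: limit the denominator to patients who had surgery, and list grade 3 or worse events after the DLT period in unoperated patients separately. This answers a narrower question, namely late toxicity after SBRT followed by surgery.

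Under either option, state whether exploration without resection counts as surgery, and report the number of patients with a window at each dose level.

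The change is mainly one of wording. For operated patients the window closes about 5–6 weeks plus 6 months (about 26 weeks) after SBRT, that is at 31–32 weeks. An equivalent close fits within the 36 weeks on study from registration if SBRT is finished within about 4–5 weeks of registration. The same limit already applies to operated patients. The article gives no assessment schedule for late toxicity in unoperated patients, so the full protocol should be checked for one. The main downside is that the reported rate may become less favourable.

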## Methods/Design

### Study design

The SPARC trial is a phase I dose-escalation study using the rolling six design [37] to establish MTD of SBRT delivered in the pre-operative setting for borderline resectable pancreatic cancers. This method minimises delays in the dose escalation phase [37]. Patients will complete SBRT in approximately one week and surgery will take place 5–6 weeks after radiotherapy. Patients will be on the study for 36 weeks from registration to end of treatment visit followed by standard care for two years post SBRT day one for the last patient, or when all participants have died.

The trial opened in April 2015 and will recruit up to 24 patients from five UK centres (Oxford, Glasgow, Leeds, Newcastle and Nottingham). The SPARC trial is conducted in accordance with the Helsinki Declaration (1996) and the regulatory requirements for clinical trials of an investigational medicinal product under the European Union Clinical Trials Directive. The trial is approved by the National Research Ethics Service Committee South Central – Oxford B (REC reference: 15/SC/0059) and is sponsored by the University of Oxford, with funding from Cancer Research UK. Data submission for the SPARC trial is via electronic submission into the online database system OpenClinica by site staff. The Oncology Clinical Trial Office (OCTO) coordinates and manages the trial while the Centre for Statistics in Medicine (University of Oxford) will perform all statistical analysis.

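### The PFS definition contradicts itself: progression counts as an event, but the censoring condition names death only, and the censoring date is last known follow-up

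*Protocol article*

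**What the plan says.** All of the definitions are in the protocol article, under Outcome measures and definitions.

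- PFS event: "PFS is defined as the time from date of first SBRT dose to the first date of progression or death for any cause".
- PFS censoring, in the same sentence: PFS "is censored at the date of last known follow-up date if they are not observed to die during the course of the trial".
- OS, in the next sentence, runs from the same start to death from any cause, and patients without that event are censored when last known to be in follow-up.

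Statistical analysis sets the outputs: "Both PFS and OS estimates at one and two years and 90 % CI will be provided together with median estimates". It adds a Kaplan-Meier curve and refers to a statistical analysis plan that is not shown.

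Study design puts patients on study for 36 weeks from registration to the end-of-treatment visit, "followed by standard care for two years post SBRT day one for the last patient, or when all participants have died". Sample size considerations gives a maximum of 24 evaluable patients.

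**The concern.** The event clause and the censoring clause should divide patients into two groups that do not overlap. Here they overlap. A patient with dated progression who is still alive at last follow-up has an event under the first clause and is censored under the second. The condition on death alone is the one that belongs to OS.

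If the censoring clause were applied as written, a progression would count only if the patient later died. The longest survivors after progression would then be entered as progression-free up to last contact. That moves the PFS curve upwards, towards OS, and most at the later of the two reported time points.

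A second problem remains even if the condition is read as covering progression as well as death. Censoring is at last known follow-up, not at the last assessment that showed no progression. Once trial visits give way to standard care, the last contact may establish only that the patient is alive. Keeping such a patient in the risk set after the last disease assessment adds time at risk during which progression may have gone unseen.

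**Working it through.** **Reading the text.** Classify each type of patient at last follow-up under the two clauses.

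| Status at last follow-up | Event clause | Censoring clause |
|---|---|---|
| Died, with or without earlier progression | Event at the first of the two | Does not apply |
| Alive, no progression | No event | Censored |
| Alive, has progressed | Event at progression | Censored at last follow-up |

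Only the third row conflicts. Patients who progress and later die are events at progression on either reading. The article states no PFS figure, so there is none to reproduce.

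**Size if the censoring clause is applied literally.** Inputs:

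- Median OS of 16.4 months, from the retrospective SBRT series of borderline-resectable patients described in the Discussion.
- Median PFS of 8, 10 or 12 months. This is an assumption; the article gives no PFS figure.
- Exponential time to progression and exponential survival after progression, the latter tuned so that median OS is 16.4 months. Every patient is taken to progress before death. These are assumptions.
- Follow-up spread uniformly over 24 to 48 months, or exactly 24 months for all. The first is closer to the Study design text, but its upper end is an assumption.

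With progression always an event, PFS at t months is 2^(−t/median). At 24 months this gives 2^(−24/8) = 12.5%, 2^(−24/10) = 18.9% and 2^(−24/12) = 25.0%.

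The literal rule was simulated with 400,000 patients per scenario. A patient dead by last follow-up is an event at progression, and a patient alive is censored at last follow-up. The Kaplan-Meier estimate was read just before 24 months (at 23.9). Both rules were run on the same simulated patients, so the progression-as-event column differs slightly from the formula.

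| Follow-up | Median PFS assumed | Progressed and alive at last follow-up | 24-month PFS, progression as event | 24-month PFS, literal rule | Excess (points) | Median under literal rule |
|---|---|---|---|---|---|---|
| 24–48 months | 8 | 8.6% | 12.7% | 18.2% | 5.5 | 8.3 |
| 24–48 months | 10 | 6.1% | 19.1% | 22.0% | 2.9 | 10.2 |
| 24–48 months | 12 | 4.1% | 25.2% | 26.4% | 1.2 | 12.1 |
| 24 months for all | 8 | 17.3% | 12.5% | 29.8% | 17.3 | 9.2 |
| 24 months for all | 10 | 11.9% | 19.1% | 30.9% | 11.8 | 10.7 |
| 24 months for all | 12 | 7.5% | 25.1% | 32.5% | 7.4 | 12.3 |

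At 12 months the excess is 0.1 to 2.2 points with 24–48 months of follow-up (for example 37.5 − 35.3 = 2.2), and 0.7 to 6.8 points with 24 months for all (42.1 − 35.3 = 6.8).

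In patients, with 24 treated and 24–48 months of follow-up, the conflict touches about 24 × 0.041 = 1.0 to 24 × 0.086 = 2.1 people.

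**Set against precision.** For a two-year estimate of 20% in 24 patients, ignoring censoring, the standard error is √(0.20 × 0.80 / 24) = 0.082. The 90% half-width is 1.645 × 0.082 = 0.13, or about 13 points.

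**Censoring date.** This cannot be quantified. The article does not give the schedule of disease assessments after the 36-week visit.

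**The case against.** The best defence is that the sentence gives the event first and offers censoring as the alternative to it. A patient with dated progression already has a PFS time, and nothing gives the censoring clause precedence. That is the natural reading, and under it this part of the wording biases nothing. This stands. It does not remove the defect, because the article states an explicit censoring condition that gives a different answer for the same patient. That is not a detail left to the analysis plan, and a plan drafted from this sentence could carry the condition over.

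A reader might infer three stronger things that the document does not support:

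- **That PFS will be overstated.** This follows only if the censoring clause overrides the event clause, which the text does not say.
- **That 24-month PFS becomes equal to OS.** This needs the literal rule and every patient followed for exactly 24 months. Study design runs follow-up to two years after the last patient's first SBRT day, and the Discussion reports one recruit in the first year, so earlier patients are followed for longer.
- **That these PFS estimates will set up the phase II study.** The Conclusion makes phase II follow from the MTD and leaves definitive evaluation of efficacy to that study.

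On the censoring date, it can fairly be said that this convention is often settled in the analysis plan, and that standard care need not mean an absence of disease assessment. Both remarks limit what can be claimed about size. They do not change the fact that the article fixes a date, and that this date can credit progression-free time to a patient known only to be alive.

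It is also true that an excess of 1 to 6 points lies well inside a 90% half-width of about 13 points, and that PFS here is a descriptive secondary outcome with no stated threshold.

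**Conclusion.** The concern holds as an internal contradiction in the PFS definition, not as a demonstrated bias. On the event-first reading there is no bias from the death-only condition. On the literal reading, 24-month PFS is overstated by roughly 1 to 6 percentage points with follow-up spread over 24 to 48 months, and the median by 0.1 to 0.3 months. If follow-up stopped at 24 months for all, the 24-month excess would be about 7 to 17 points. These figures rest on the 16.4-month median OS from a retrospective series, on assumed PFS medians of 8 to 12 months and on exponential times, so they show a range and are not a forecast for this trial.

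The choice of last known follow-up as the censoring date is a separate weakness that remains on either reading; its size is unknown. The primary endpoint, the escalation rules and the sample size are untouched. Severity is minor to moderate.

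**What to change.** Replace the PFS censoring clause, in the protocol and in the analysis plan if it carries the same wording, with: *patients with neither documented progression nor death are censored at the date of their last disease assessment showing no progression*. Keep last known follow-up as the censoring date for OS only.

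This makes events and censoring mutually exclusive and stops contact that shows only survival from counting as progression-free time. The cost is one sentence and possibly slightly less favourable PFS estimates. OS, the MTD and the sample size do not change.
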